#### Other measures

*Disease severity *of the TFJ from weight bearing anteroposterior knee x-rays taken at screening will be determined using the Kellgren and Lawrence grading system [23] where 0 = normal; 1 = possible osteophytes; 2 = minimal osteophytes and possible joint space narrowing; 3 = moderate osteophytes, some narrowing and possible sclerosis and; 4 = large osteophytes, definite narrowing and severe sclerosis. PFJ OA will be assessed from a skyline x-ray using a radiographic atlas [22]. The medial and lateral PFJ compartments will each be scored separately for the presence of osteophytes and joint space narrowing where 0 = normal; 1 = mild or 1–33% abnormal; 2 = moderate or 34–66% abnormal and; 3 = severe or 67–100% abnormal. *Co-interventions, adherence and adverse effects will also be recorded*. Participants will be asked to refrain from other forms of OA treatment, but stable drug doses will be permitted. Physiotherapists will record attendance, details of treatment progression (physiotherapy group) and adverse events. Participants will record adherence with home exercises (physiotherapy group), adverse events and any co-interventions, including knee-related medication use in a log-book.

### Interventions

Each participant will be treated by an experienced and registered physiotherapist. Treating practitioners will be trained and proficient in both of the interventions (physiotherapy and education control). Each treatment will be delivered in 8 sessions over 12 weeks (once per week for four weeks, then once every two weeks for 8 weeks). Reasonable costs associated with treatments will be met by the project.

#### Physiotherapy Treatment

The physiotherapy treatment will be similar to that employed in our previous RCTs for patellofemoral pain in younger people [19,20]. Treatment will consist of (i) functional retraining exercises for the quadriceps muscle; (ii) quadriceps and hip muscle strengthening; (iii) patellar taping; (iv) manual PFJ and soft tissue mobilisation; and (v) OA education. The treatment will be tailored according to each participant's clinical presentation (eg strength, pain severity, swelling) as well as the presence of co-morbidities (eg back and hip pain or pathology), and will be progressed based on individual response to exercise load, thus optimising treatment effects. Exercises will be taught and supervised by the physiotherapist during each visit. A home exercise program will be prescribed, to be performed independently at home 4 times per week. An exercise manual for participants will be produced, with clear instructions and diagrams to ensure correct and safe performance of exercise. Specific aspects of the treatment are outlined in Table 2 and will include:

**Table 2 T2:** Physiotherapy treatment components

**Functional retraining exercises^† ^performed four times/week – participants perform a contraction of medial quadriceps in two of the following functional activities**	
- sitting (isometric)	
- sit-stand	
- step up	
- single leg squat	
**Quadriceps muscle strengthening^† ^performed four times/week – participants complete one exercise in each of the following**	
- inner range (open kinetic chain)	
- mid range (open kinetic chain)	
- weight-bearing (wall squat)	
**Hip abduction strengthening^† ^performed four times/week**	
- sidelying hip abduction	
**Patellar taping**	
- combination of tilt, medial glide and fat pad unloading – tape will be applied by the physiotherapist at each visit, worn continuously for one week and then removed	-
**Patellofemoral and soft-tissue mobilisation**	
- mobilisation of the patella (medial glides) performed by the physiotherapists	
- massage to the painful and tight soft tissue structures, performed by the physiotherapist	

^†^Exact exercise and its number of repetitions will be determined by the physiotherapist from a schedule of permissible exercises based on each participant's clinical presentation (eg strength, pain severity, swelling), presence of comorbidities (eg back and hip pain or pathology) and will be progressed based on individual response to exercise load

(i) Functional retraining exercises for the quadriceps muscle. The muscle retraining is designed to enhance the co-ordination (magnitude and onset timing) of the medial quadriceps, relative to the lateral utilising biofeedback within the sessions. In order to accommodate a patient group with heterogeneous symptoms, the functional retraining exercises may be performed statically and/or dynamically during various functional activities (eg step up, step down, sit to stand).

(ii) Quadriceps and hip abduction strengthening. The exercise selection will be based on baseline capacity of the individual and then progressed, based on response to exercise load, thus maximising the training effects. Resistance will be provided by weights, rubber tubing and/or body weight.

(iii) Patellar taping to reduce pain using the same standardised protocol as per our previous knee OA research [30,31]. The tape will be applied by the physiotherapist at each visit, worn continuously for one week and then removed.

(iv) Manual PFJ and soft tissue mobilisation, comprising medial patellar glides and massage to the lateral soft tissue structures, performed by the physiotherapist.

(v) OA education covering topics such as exercise, diet, weight loss etc.

Following cessation of supervised physiotherapy sessions at 12 weeks, participants will be instructed to continue with a home exercise program. Adherence to the program will be monitored from the diary recordings of exercise completions.

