### Procedure

The randomisation schedule (permuted blocks of 8 to 12) will be generated and maintained centrally by one of the investigators (BV), who will not be involved in assessment of participants. The randomisation schedule will be revealed via telephone following baseline assessment. A blinded investigator will perform outcome assessments (Table 1) at baseline, 12 weeks and 9 months, and participants will be instructed not to divulge their group allocation. Security of the blinding system will be evaluated to ensure integrity.

**Table 1 T1:** Outcome measures used in the randomised controlled trial

**Primary Outcome**	**Measurement**
Usual pain on movement in the previous week	0–100 mm visual analogue scale (VAS) with terminal descriptors: 0 = no pain; 10 = maximal pain
Usual pain during nominated aggravating activity in the previous week	0–100 mm visual analogue scale (VAS) with terminal descriptors: 0 = no pain; 10 = maximal pain
Self reported difficulty with physical function	Physical Function subscale of the Western and Onatario MacMasters University (WOMAC) Osteoarthritis Index (Likert version)

**Secondary Outcomes**	**Measurement**

*Symptoms*	
Pain and stiffness	Pain and Stiffness subscales of the WOMAC
Perceived global effect score	5 point ordinal scale (1-much improved; 2-improved. 3-same; 4-worse; 5-much worse)
Sports and recreation function	Sports and recreation function dimension of the Knee Injury and Osteoarthritis Score (KOOS)
Symptoms	Symptoms dimension of the KOOS
Knee related quality-of-life	Knee related quality-of-life dimension of the KOOS
*Function*	
Lower extremity functional performance	One-leg rise test – maximum number of one-leg rises from sitting on a 0.48 m stool
Stair ambulation performance	Timed stair ascent and descent
Standing balance	Step test – number of times can step foot up and down off 15 cm step in 15 s

**Other Outcomes**	**Measurement**

Physical activity levels	Physical Activity Scale for the Elderly (PASE)
Adherence (physiotherapy group only)	Number of physiotherapy visits Completion of home exercises via log-book
Knee-related medication use	Log-book
Adverse effects	Log-book and open probe questioning

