#### Secondary outcome measures

*Pain and stiffness *will be assessed using the relevant subscales of the WOMAC [25]. Participants will rate their perceived overall change in symptoms following treatment on a 5 point ordinal scale: 1-much improved, 2-improved, 3-no change, 4-worse, 5-much worse, giving a *perceived global effect score*. *Sports and recreation function, symptoms *and *knee-related quality-of-life *will be assessed using the relevant dimensions of the Knee Injury and Osteoarthritis Outcome Score (KOOS) [26].

*Objective measures of function *will include the one-leg rise test, a timed stair ambulation test and the step-test. The one-leg rise test is the maximum number of one-leg rises the participant can perform from sitting on a stool. The participant must hold their non-test leg out straight and cannot use their arms for assistance. The number of rises that the participant can complete will be recorded. This test is a measure of lower extremity functional performance that has been found to predict the development of radiographic knee OA in middle aged people with chronic knee pain [27]. The timed stair ambulation task involves the participant ascending and descending a set of nine standard steps at their usual pace and the total time taken recorded, with longer time taken indicating poorer physical function [28]. The step-test is a functional, dynamic test of standing balance, where the participants stands on one leg in front of a 15 cm step, and places the opposite foot on and off the step as quickly as possible over 15 seconds. The total number of successful steps are recorded, with higher scores indicating better balance [29].

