#### Physiotherapy Education Control

In order to control for the psychosocial contact inherent with the physiotherapy treatment, participants allocated to the control group will attend individualised OA education sessions covering topics such as exercise, diet, weight loss, etc, provided by the physiotherapist with the same frequency as the physiotherapy sessions.

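### Tape from the last physiotherapy visit may still be on, or just coming off, at the 12-week assessment in one arm only, and nothing stated conceals it from the blinded assessor

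*Protocol article*

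**What the plan says.** All references are to the Methods of the protocol article.

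- **Taping** (Physiotherapy Treatment, item iii; Table 2 says the same): "The tape will be applied by the physiotherapist at each visit, worn continuously for one week and then removed".
- **Control arm** (Physiotherapy Education Control): "participants allocated to the control group will attend individualised OA education sessions covering topics such as exercise, diet, weight loss, etc". The visit frequency matches the physiotherapy arm; no tape is described.
- **Visits** (Interventions): eight sessions over 12 weeks, "once per week for four weeks, then once every two weeks for 8 weeks".
- **End of supervised treatment** (end of Physiotherapy Treatment): "Following cessation of supervised physiotherapy sessions at 12 weeks, participants will be instructed to continue with a home exercise program".
- **Assessment** (Procedure): "A blinded investigator will perform outcome assessments (Table 1) at baseline, 12 weeks and 9 months".
- **Protection and check of blinding** (Procedure): "participants will be instructed not to divulge their group allocation", followed by "Security of the blinding system will be evaluated to ensure integrity".
- **Tests recorded by the assessor** (Secondary outcome measures): one-leg rise, timed stairs and step test. For the first, "The number of rises that the participant can complete will be recorded".

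**The concern.** Tape on the knee marks the physiotherapy arm. If it is present when the assessor meets the participant, allocation can be read without a word being spoken, and asking participants to keep silent does not help.

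Participants and treating physiotherapists know which treatment is given, so the assessor is the party whose blinding supports the single-blind description. Assessor blinding matters most where the assessor counts or times: deciding whether a rise or a step was completed, and when to start and stop the clock. An assessor who knows the arm may make these calls differently, which is detection bias. The tests at stake belong to the trial's stated secondary aim, and 12 weeks is the end-of-treatment time point.

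**Working it through.** The question is whether the stated tape duration, visit schedule and assessment time overlap.

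**Inputs.** Four weekly sessions, then fortnightly sessions for 8 weeks (Interventions); tape worn for 1 week after each visit (Physiotherapy Treatment); assessment at week 12 (Procedure).

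**The plan's own figure.** Sessions = 4 + 8/2 = 8. This reproduces the stated eight.

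**Overlap.** Tape off = last visit + 1 week. Tape-free gap = 12 − (last visit + 1). The article does not list visit weeks, and three layouts give eight sessions:

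| Layout | Visit weeks | Last visit | Tape off | Tape-free gap before week 12 |
|---|---|---|---|---|
| A | 1, 2, 3, 4, 6, 8, 10, 12 | 12 | 12 + 1 = 13 | 12 − 13 = −1 week (still on) |
| B | 0, 1, 2, 3, 5, 7, 9, 11 | 11 | 11 + 1 = 12 | 12 − 12 = 0 (coming off) |
| C | 0, 1, 2, 3, 4, 6, 8, 10 | 10 | 10 + 1 = 11 | 12 − 11 = 1 week (off) |

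**Which layout fits best.** The article places the end of supervised sessions at 12 weeks. Layout A matches this directly, B is a week short and C two weeks short. Under A, tape is on if the assessment follows the last visit by less than a week. That gap is not stated.

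**What the safeguards do.** The instruction to participants covers speech only. The evaluation of blinding is a check that can show afterwards that blinding was lost; it does not keep it.

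**Which outcomes are exposed.**

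- Primary outcomes (two pain scales and WOMAC physical function): rated by the participant, so what the assessor sees does not change who rates them.
- Self-reported secondary outcomes (WOMAC pain and stiffness, global effect, KOOS dimensions): the same.
- One-leg rise, timed stairs, step test at 12 weeks: counted or timed by the assessor, hence exposed.
- The same three tests at 9 months: the latest clinic-applied tape is off by week 13, so not exposed by this route.

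**The case against.** **Timing is inferred.** Layout C fits the wording of the visit schedule and leaves a tape-free week, and under B the tape is due off at the nominal assessment time. Ending sessions at 12 weeks can also mean the end of a 12-week programme rather than a visit in that week. This stands. A reader might infer that every physiotherapy participant is taped at the assessment whatever the schedule; the article does not support that.

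**Visibility is assumed.** The article does not say that knees are bare, and none of the three tests as described needs an exposed knee. This also stands: visibility is a risk, not a fact. Clothing rules are the kind of detail that a journal article may leave to the full protocol, so silence about clothing alone would be no finding. The point rests instead on elements the article does fix: one-arm taping for a week, sessions ending at 12 weeks, and a blinded assessment at 12 weeks.

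**Blinding is to be evaluated.** Correct, and the instruction to participants should not be called the only blinding measure. But the evaluation does not prevent unblinding.

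**The consequence is limited.** A reader might infer that the single-blind claim fails, or that the primary comparison is biased. Neither follows. The primary outcomes are self-reported by participants who know what treatment they receive, so assessor unblinding does not alter how they are obtained. Overlap of tape with the one-week pain recall period is a separate matter that does not concern assessor blinding.

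**Conclusion.** The point holds as a risk to assessor blinding, limited to three secondary performance tests at 12 weeks. On the reading closest to the text, tape is on or just coming off at that assessment in the physiotherapy arm and absent in the control arm, and no stated measure conceals it.

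The conclusion assumes that the last supervised visit falls at about week 11 or 12, that the assessment follows the last visit within the period of tape wear or at its end, and that the knee is not already covered. If layout C was intended, or if knees are covered under a rule not shown here, the risk from tape on the knee largely disappears. The size of any bias in the three tests cannot be calculated from the article. Sample size and power are not affected.

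**What to change.** 1. Add to the assessment procedure that, at the 12-week visit, participants in both arms cover both knees (long trousers or identical opaque sleeves) before meeting the assessor. This is not needed at baseline, because allocation is revealed only afterwards.
2. Have the assessor record a guess of allocation at the 12-week visit and report it by arm. This gives a method to the evaluation of blinding already promised under Procedure.
3. Reconcile Procedure, Interventions and Physiotherapy Treatment on the timing of the 12-week assessment relative to the last visit, so that tape status at assessment is known.

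None of this changes the taping or the treatment schedule. The cost is about a line of text on covering the knees, one extra item on the assessment form, a clarified timing statement and the minor inconvenience of covering the knees. No extra staff are needed.

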#### Physiotherapy Education Control

In order to control for the psychosocial contact inherent with the physiotherapy treatment, participants allocated to the control group will attend individualised OA education sessions covering topics such as exercise, diet, weight loss, etc, provided by the physiotherapist with the same frequency as the physiotherapy sessions.

### Data quality and management

Strategies employed to ensure data quality include: (i) training of assessors and physiotherapists; (ii) assessment of procedural quality; (iii) random checks by investigators of adherence to study protocols; and (iv) random checks of forms for completeness and data for accuracy. All analyses will be conducted on an intention-to-treat basis. The primary outcomes measured at 12 weeks and 9 months will be analysed using linear mixed regression models, including their respective baseline scores as a covariate, subjects as a random effect, treatment condition as a fixed factor and the covariate by treatment interaction. Participant characteristics (eg; gender, radiographic severity of TFJ and PFJ OA) will also be included as covariates. Regression diagnostics will be used to check for normality of the measures and homogeneity of variance, where appropriate. Comparisons between group means will be performed using Bonferroni or Newman Keuls range tests. An alpha level of 0.05 will be used. Calculation of the number needed to treat index will be performed to facilitate the development of clinical guidelines.

## Discussion and Conclusion

PFJ OA is emerging as a distinct clinical entity that is common, is associated with considerable pain and disability, and is an important and novel area of research, since little is known about the optimal management of this condition. This study uses a single-blind RCT design to investigate whether a multimodal physiotherapy treatment, targeted to the PFJ, is more effective in reducing pain and improving physical function than a physiotherapy education control intervention in people with PFJ OA. As a secondary aim, it will evaluate whether the targeted physiotherapy treatment results in greater perceived improvement, self-reported stiffness, pain, sport and recreational function, symptoms and knee-related quality of life, as well as performance on functionally relevant tasks (one-leg rises, timed stair ambulation, and step-test) than the physiotherapy education control intervention.

In contrast to OA primarily affecting the TFJ, comparatively little known about the features or impairments associated with OA of the PFJ, and hence designing a targeted intervention is challenging. Thus, we have chosen to investigate a physiotherapy intervention that is largely based on a program that we have previously found to be successful in younger people with PFJ pain (patellofemoral pain syndrome) [19,20]. Components of this targeted intervention include: (i) functional retraining of the quadriceps muscle; (ii) quadriceps and hip muscle strengthening; (iii) patellar taping; (iv) manual PFJ and soft tissue mobilisation; and (v) OA education. This intervention is currently considered to be "best-practice" in the management of PFJ pain, and is increasingly being employed clinically in the management of people with PFJ OA.

An impairment that has been the subject of recent evaluation in participants with generalised knee OA is patellar malalignment. Patellar malalignment is typically exhibited as lateral patellar tilt, displacement or subluxation and may be important in PFJ OA by reducing and lateralising the PFJ contact area [32], thus increasing stress in this compartment. In people with knee OA, PFJ malalignment has been shown to be associated with indices of OA (joint space narrowing and loss of cartilage thickness) [33,34] as well as progression of OA (joint space narrowing) [35] in the PFJ compartment and increased functional impairment [36]. Thus, PFJ malalignment is a key feature of PFJ OA that could be amenable to a targeted intervention such as physiotherapy. This supports the inclusion of patellar tape in our targeted treatment, since it has the potential to reduce patellar malalignment [37-39] and we have already shown that patellar tape can reduce knee pain in generalised knee OA populations [30,31]. Other treatment modalities (eg PFJ and soft tissue mobilisations), may assist in the treatment of PFJ pain and malalignment in this patient population.

The balance of medial and lateral quadriceps activity is essential to maintain PFJ alignment. Experimental studies confirm that reduced or delayed medial quadriceps activity (relative to the lateral quadriceps) increases lateral patellar malalignment, leading to areas of heightened contact stress across the lateral PFJ compartment [40,41]. Thus, the balance of muscle activation between the medial and lateral quadriceps may be important in PFJ disease. In our studies of younger people with PFJ pain [42,43], we have observed a temporal delay in medial quadriceps activity. Thus, it is likely that individuals with PFJ OA may require a specific retraining program designed to restore balanced quadriceps activity.

While the role of hip muscle function in PFJ OA has not been investigated, there is increasing evidence that hip muscle function is impaired (reduced strength [44], delayed hip muscle activity [45]; and altered hip movements during ambulation [46]) in other PFJ conditions. These studies indicate that hip abduction is particularly relevant in patients with PFJ pain and hence, this study is focusing on strengthening hip abduction. Furthermore, the inclusion of a hip abduction strengthening program in this study reflects contemporary clinical practice.

While the main goal of treatment for OA is to reduce pain and disability, it is not known how non-pharmacological interventions achieve this goal; such is the complex multi-factorial nature of OA pain. Our intervention is based on reversing the compartment-specific impairments *likely *to be associated with PFJ OA. Furthermore, this intervention builds on our previous studies, which have established that: (i) taping the patella medially reduces pain and disability associated with non-specific knee OA [30,31,47] and may reduce PFJ malalignment [48] and (ii) a quadriceps retraining program can reduce pain and disability, as well as restore quadriceps muscle activation patterns in younger people with PFJ pain [19,49,50]. Our unique RCT is targeting PFJ OA, an important sub-group of knee OA, with a specifically designed intervention. The project's outcome will influence knee OA rehabilitation, thus reducing the personal and societal burden of this increasing public health problem.
